### Sample Size Calculation

In order to obtain mid-term results, a 5-year follow-up period has been selected, consistent with standard practices in Dutch metabolic bariatric surgery. A total of 63 patients per group is necessary to detect a 5% difference %TWL between groups 5 years post-surgery. This calculation is performed using PASS software, with parameters set at power = 80%, alpha = 0.05, standard deviation = 10%, and average %TWL of group 1 vs. group 2 being 32 vs. 27, assuming a two-sided independent *t*-test.

Jense et al. observed a loss-to-follow-up (LtfU) ranging from 21 to 58% three to five years postoperatively [21]. To have sufficient power for the 5-year analysis, this study takes into account a LtFU of 40%, assuming that actively contacting patients will reduce LtFU at 5 years postoperatively. Based on a required sample of 63 individuals per group and an expected LtFU of 40%, we aim to include 210 patients for this study, 105 per group.

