### Secondary Outcomes

%EWL: defined as the percentage of excess weight lost relative to the excess weight at the time of informed consent [22]. In formula$${\%EWL}=\frac{\text{preoperative BMI}-\text{ current BMI}}{\text{preoperative BMI}-25}\text{x}\;100$$Reduction or remission of obesity complications: Obesity complications include type 2 diabetes mellitus, hypertension, joint complaints, dyslipidemia, OSAS, and GERD. (Inter)national guidelines are used as reference [23, 24]. Reduction is defined as a decrease in symptoms, medication use and/or dosage, and/or laboratory results. Remission is defined as the state in which a patient no longer reports symptoms, does not require any medication for their comorbidity, and/or has normalized laboratory results. In case of type 2 diabetes, remission is defined if glycosylated hemoglobin (HbA1c) is 43 mmol/mol without the use of pharmacotherapy as per local protocol [23] In case of OSAS, remission is considered when there is a discontinuation of CPAP treatment.Quality of life: assessed using the SF-36, OBESI-Q, and GERD-HQoL questionnaires at earlier mentioned follow-up intervals compared to pre-operative baseline measurements.Presence of early and late dumping: determined based on symptoms reported by patients and evaluated by expert physicians during the follow-up period.Complications: All complications during follow-up and until 5 years postoperative are included in the analysis, regardless of their potential relation to the ring. Complications are categorized as perioperative, early (< 30 days, with or without readmission), and late (> 30 days, with or without readmission). Possible complications include bleeding, wound infections, intra-abdominal abscesses, anastomotic leaks, deficiencies (especially in vitamin B12 and ferritin), conversions, migration, erosion, and slipping of the ring. Laboratory reference values are used for deficiencies.

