### Statistical Analysis

IBM’s Statistical Package for the Social Sciences (SPSS) is utilized for the statistical analyses of the obtained data. Histograms (visual inspection) are used to ascertain whether variables are normally distributed. A significance level (alpha) of 0.05 is applied to all analyses unless stated otherwise. Differences in baseline characteristics of the study groups are tested using the independent *t*-test (for continuous, normally distributed data), the Mann–Whitney test (for non-normally distributed or ordinal data), or the chi-square test (for categorical data).

Assumptions for linear regression will be checked for all outcomes, including normality of residuals and homogeneity of variances. Where necessary, transformations (e.g., log transformation) were applied to meet model assumptions.

Difference between groups in %TWL, %EWL, and GERD-HRQoL at 5 years postoperative will be assessed using the independent *t*-test or Mann–Whitney test (for normally or non-normally distributed data, respectively). Baseline characteristics related to both the type of surgery and outcome variables (with *p*-value < 0.15) will be considered confounders in the analyses. If one or more confounders are identified, linear regression models will be used to assess differences between groups in %TWL, %EWL, and GERD-HRQoL at 5 years postoperative, each adjusted for relevant confounders.

The difference between groups in the reduction of obesity complications at 5 years postoperative will be tested using chi-square tests for each comorbidity. Holm-Bonferroni correction will be used to correct for multiple testing.

Chi-square tests will be used for the difference between groups in change of scores of the questionnaires, early and late dumping, and reflux. Additionally, a linear mixed model analysis will test the difference in change in the subscales of the SF-36 and OBESI-Q over time between groups.

The difference in the total number of complications between groups will be tested with independent *t*-tests or Mann–Whitney tests (for normally or non-normally distributed data, respectively).

Missing data will be reported if known. A sensitivity analysis will be performed for the primary outcome: analysis of the data “as-is” (without imputation) will be compared with the results of the analysis where missing data is imputed.

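### Late complications are compared as raw counts with no time at risk, although 40% loss by 5 years is planned: the 5-year burden is understated, and unequal retention, if it occurs, would distort the comparison

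*Protocol article*

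**What the plan says.** Three parts of the protocol article bear on this.

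- **Secondary Outcomes** sets the window: "All complications during follow-up and until 5 years postoperative are included in the analysis". Complications are classed as perioperative, early (under 30 days) and "late (> 30 days, with or without readmission"). The examples mix events expected soon after surgery (bleeding, wound infection, leaks) with events that can occur at any time (deficiencies; migration, erosion and slipping of the ring).
- **Sample Size Calculation** states that "this study takes into account a LtFU of 40" per cent, against a cited study with loss "ranging from 21 to 58% three to five years postoperatively".
- **Statistical Analysis** fixes the test: "The difference in the total number of complications between groups will be tested with independent" *t*-tests or Mann–Whitney tests, depending on normality.

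Dumping is "determined based on symptoms reported by patients and evaluated by expert physicians during the follow-up period", and its test is given in one sentence: "Chi-square tests will be used for the difference between groups in change of scores of the questionnaires, early and late dumping, and reflux". The only missing-data sensitivity analysis is for the primary outcome. Follow-up time, rates and censoring are not mentioned for any safety outcome.

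**The concern.** A patient lost at 1 year without a complication scores zero, the same as a patient followed for 5 years without one. The first has been observed for a fifth of the time. Two things follow for late complications.

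First, the mean count per patient falls short of the 5-year burden in both arms, however evenly patients are lost. Second, if one arm is followed for longer, it records more events at the same true rate; if the ring arm is followed for less time, a real excess can disappear. This is the trial's planned comparison of harm for an implanted device, and the trial is non-blinded, so different retention by arm cannot be excluded.

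The article names the tests itself, so this is a stated choice and not detail left to a fuller document.

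**Working it through.** **The plan's own figure.** With a difference of 5, SD 10, two-sided alpha 0.05 and 80% power, n = 2 × (1.96 + 0.84)² × 10² / 5² ≈ 62.7, so 63 per group. With 40% loss, 63 / 0.60 = 105 per group, 210 in total. This reproduces. The same 40% is applied to both arms.

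**Assumptions.** The document gives no complication rate, dropout pattern or loss by arm. I assume a constant dropout hazard h reaching loss p at 5 years, a constant late-event rate, 105 patients per arm and, in the simulations, gamma between-patient variation with dispersion 0.5 unless stated otherwise.

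**Follow-up actually observed.** h = −ln(1 − p)/5; mean follow-up = (1 − e^(−5h))/h = p/h.

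| Loss by 5 years | Mean follow-up (years) | Share of 5 years |
|---|---|---|
| 30% | 4.21 | 84% |
| 40% | 3.92 | 78% |
| 50% | 3.61 | 72% |

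At 40% loss, about 22% of time-proportional late events go unseen. The pattern of loss matters: uniform loss gives 1 − 0.40/2 = 80%, and loss concentrated in the later years about 85%.

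**First-event risk.** With event hazard λ, the crude proportion is λ/(λ + h) × (1 − e^(−5(λ + h))). At 40% loss a true 5-year risk of 20% appears as 15.8%, and 30% as 23.8%.

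**Equal loss, equal true rates.** With 40% lost in both arms, simulated error of the *t*-test and Mann–Whitney test was 4.3–5.7% (Poisson counts).

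**Unequal loss, equal true rates, late events only.** At 30% versus 50%, the count ratio is 4.21/3.61 = 1.17. False positives:

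| Late events per patient-year | *t*-test | Mann–Whitney |
|---|---|---|
| 0.1 | about 8% | about 9% |
| 0.2 | 11–12% | 13–14% |
| 0.4 | 16–17% | 19–20% |

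A negative binomial model with a log follow-up offset gives 4.5–6%. At 35% versus 45% loss the planned tests give about 6–9%. Without the extra between-patient variation, 30% versus 50% gives 10–27%.

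**Masking.** Take a true rate ratio of 1.5, a control mean of 0.5 events over 5 years (Poisson), and 50% loss in the higher-rate arm against 30%. The count ratio shrinks to 1.5 × 3.61/4.21 ≈ 1.29. Power is about 21% (*t*-test) and 18% (Mann–Whitney), against 51% for a person-time rate ratio. With equal 40% loss the three figures are 49%, 44% and 53%.

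**Early events in the total.** Suppose 0.5 early events per patient plus 0.1 late per year, so about half are early. At 30% versus 50% loss the count ratio is (0.5 + 0.421)/(0.5 + 0.361) = 1.07, and the planned tests give about 6–7% error. An offset on that same total goes wrong the other way. The crude rates are 0.921/4.21 = 0.219 and 0.861/3.61 = 0.239, a spurious ratio of 1.09 against the arm lost sooner. Across simulated settings with half or more of events early, the offset model on the total gave about 10–22% false positives. On late events only, it stayed at about 4–6%.

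**The case against.** The strongest objection is that the planned comparison is adequate in the situation the document describes. The plan applies one loss figure to both arms, and with equal loss the tests hold their level. Lack of blinding makes unequal loss possible but not expected. Early complications happen while follow-up is nearly complete, and if they make up about half of the total the planned tests stay near 5% even at 30% versus 50% loss. All of this stands.

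It does not remove two things. Crude late counts still understate 5-year harm under equal loss, and nothing in the plan protects the late comparison if retention differs. It may be said that the section specifies a test, not an estimate of incidence. But a raw late count after 5 years of planned follow-up will be read as one.

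Some stronger readings are tempting and not supported:

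- *Incomplete follow-up by itself creates a false difference between arms.* It does not; that needs unequal loss.
- *The cited 21–58% range shows how far the arms might differ.* The document gives it as a range over three to five years after surgery, not as a contrast between arms.
- *Dumping is certainly affected.* The Secondary Outcomes wording could mean ever/never during follow-up. The Outcome Measurement section, however, has all outcomes measured at 4 months and annually, so the chi-square test may compare presence at a visit. Person-time does not enter that comparison.
- *An offset on the total would cure the problem.* With early events included, it introduces a bias of its own.

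**Conclusion.** The point holds for late complications. As written, the analysis would capture roughly 78–85% of time-proportional late events at 40% loss, depending on the dropout pattern, and so understates the 5-year burden in both arms. Distortion of the comparison is conditional. At an assumed 30% versus 50% loss it amounts to a count ratio of 1.17 and about 8–20% false positives when events are late and occur at 0.1–0.4 per patient-year. It is near nominal when about half or more of the events are early, and absent when loss is equal. Event rates, dropout shape and arm-specific loss are all assumptions.

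This concerns a secondary outcome and leaves the primary analysis untouched. It should be changed because the outcome is the planned comparison of harm for an implant and the correction is cheap.

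**What to change.** Split the comparison by the categories that the Secondary Outcomes section already defines:

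1. **Perioperative and early (under 30 days):** compare as proportions or counts, with no offset.
2. **Late (after 30 days):** compare the number per patient by negative binomial regression (or Poisson with robust standard errors), with log follow-up time to last contact, at most 5 years, as offset. Report the rate ratio with 95% CI.
3. **Ring events and first late complication:** report 5-year cumulative incidence, censored at last contact, with person-years by arm.
4. **Combined total:** do not apply the offset to it.
5. **Dumping:** state which outcome is meant. If it is ever/never during follow-up, use censored cumulative incidence as in item 3. If it is presence at a given visit, the chi-square test among those assessed can stay.

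The cost is a change of wording and a little more analysis. It needs the date of each complication and of last contact, which the 30-day split and the annual visits already imply. Design, sample size and visits are unchanged. One limitation remains: loss is still assumed unrelated to future complications.

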## Data Availability

No datasets were generated or analysed during the current study.
